### Study Timeline

Enrollment is conducted from the second week of each semester or quarter until 6 weeks before final examinations week. Enrollment begins the second week of the semester to assure that past 7-day questions refer to a time of typical campus activity. When there is a campus break of 2 weekdays or longer, study visits are delayed by a week to adjust the past 7-day question time period for typical campus activity. The stop date each semester or quarter assures that the 6-week intervention is delivered while participants are still attending class on campus at least once per week.

### Sample Size

An initial sample size of 400 total (100 per group per campus) will detect a 15-16 percentage point difference in proportions with 80% power at the 0.05 level (2-sided), assuming a sample size of 380 at 6 weeks (95% retention) and 340 at 26 weeks (85% retention). This effect size is expected based on previous research on attitudes and behaviors [67]. This sample size also provides more than 95% power to detect noninferiority within a 0.5 SD margin at the 0.025 level (1-sided) or a difference in means of 0.5 SD at the 0.05 level (2-sided); 0.5 SD is considered a minimally important difference in health-related quality of life outcomes [70] and corresponds to 0.5 point difference on a 5-point scale with an SD of 1 point.

### Recruitment

Participants are recruited from each site using campus announcements, flyers, tabling, and word of mouth through campus partners.

### Assignment of Interventions: Allocation

After completing the baseline survey, participants at each site are randomized 1:1 to the two groups (TECW Ed or TECW Ed+) in blocks stratified by tobacco or cannabis user status (any use in the past 30 days: yes or no) by the project coordinator using REDCap, based on randomization tables created by the study statistician with computer-generated random numbers.

### Assignment of Interventions: Blinding

Research assistants are aware of group assignments and deliver the designated intervention. Participants are not told their group assignment. Research assistants are unaware of study hypotheses and do not see participants’ before and after survey responses. Research assistants are aware of the number of Tracker reports and their nature because providing feedback to the TECW Ed+ group is a component of the intervention.

### Data Collection and Management

At the baseline and week 2 visits, a presurvey is administered before education and a postsurvey is administered after education (plus motivational enhancement for the intervention group). Assessment windows are ±3 days for the week 1 check-in, ±1 week for the week 2 visit and week 4 check-in, ±4 weeks for the week 6 visit, and ±6 weeks for the week 26 visit.

#### Contact Attempts

We are using our proven methods for achieving over 80% retention up to 6 months, including multiple contact methods (ie, text, phone calls, emails), identifying multiple alternative contact people, and sending a digital greeting 2 months before the week 26 visit [71-74]. Up to 6 contact attempts, of alternating forms, are made. Contacting alternative contact people is the last effort to reach an unreachable participant.

#### Data Management

Participant data are collected and managed using REDCap tools that are hosted through Site 2. REDCap is a Health Insurance Portability and Accountability Act (HIPAA)–compliant, web-based application that supports data capture for research studies. All data collected are anonymous through assignment of participant ID numbers and password protected. REDCap data are stored securely on a server at Site 2. Environmental scan data are entered into Excel (Microsoft Corporation) and maintained on a shared drive.

### Statistical Methods

#### Primary Outcome

The primary outcome is change in knowledge, perceptions, and attitudes. The hypothesis that the TECW Ed+ group will demonstrate a significant increase in TECW knowledge, harm perceptions, and regulatory attitudes, and that the TECW Ed group will be noninferior to the TECW Ed+ group in these outcomes by a margin of half an SD, will be tested as follows. We will compute mean scores for change in knowledge, change in harm perception, and change in belief in each group along with 2-sided 95% CIs; a CI entirely above 0 indicates a statistically significant increase at the 5% level (2-sided). In addition, for each of these measures, we will compute the difference between the TECW Ed+ group and the TECW Ed group mean scores, along with a 1-sided 97.5% CI; a CI entirely below 0.5 SD indicates noninferiority of the TECW Ed group within a 0.5 SD margin at the 0.025 level (1-sided). We will also construct mixed-effects repeated measures models to assess knowledge, perceptions, and belief outcomes at weeks 2, 6, and 26 versus group, time, and a group × time interaction, controlling for site, tobacco or cannabis use status, demographics, and baseline level of the outcome variable.

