#### Secondary Outcomes

The secondary outcomes are behavior changes. The hypothesis that the TECW Ed+ group, compared to the treatment-as-usual TECW Ed group, will display greater usage of the TECW Tracker and stronger engagement in supporting smoke- and vape-free regulatory efforts will be tested as follows. We will compare the TECW Ed+ group and the TECW Ed group with respect to the mean number of Tracker reports between baseline and 6 weeks using a generalized linear model with negative binomial distribution and log link. We will compare the 2 groups with respect to mean engagement score at 6 weeks using a 2-sample *t* test. We will also construct generalized linear mixed-effects repeated measures models to assess TECW-related behavior outcomes at weeks 1, 2, 4, 6, and 26 versus group, time, and a group × time interaction, controlling for site, tobacco or cannabis use status, demographics, and, for engagement, baseline level of the outcome variable. As an ancillary analysis, we will assess the link between awareness of campus TECW mitigation and behavioral outcomes among participants by including awareness as a covariate in models of Tracker report behavior. All randomized participants with week 6 data will be included in primary outcome analyses, and those who completed week 6 and month 6 will be included in follow-up analyses.

As an ancillary outcome, we will evaluate spillover behaviors such as off-campus TECW advocacy, and among tobacco users, proper disposal of e-waste and reported tobacco cessation by computing frequencies and percentages for each of these behaviors overall and by site and group at 6 weeks and 26 weeks. Furthermore, to describe changes in campus TECW, we will use generalized linear mixed models of the number of TECW reports per month to estimate trends over time and association with environmental scans, overall and among study participants, assuming autoregressive correlation from month to month at each site and negative binomial distribution with log link. Separate models will be created for different types of TECW, and interactions between site and time will be included to assess differences in trends between sites.

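### The tests that decide the noninferiority and engagement hypotheses omit covariates the trial already holds; the loss falls mainly on week-6 engagement

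*Protocol article*

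**What the plan says.** **Primary outcomes** (Statistical Methods, Primary Outcome). The outcome is defined as change: "The primary outcome is change in knowledge, perceptions, and attitudes". Each arm's mean change is first compared with zero through a two-sided 95% interval. Between arms, "we will compute the difference between the TECW Ed+ group and the TECW Ed group mean scores, along with a 1-sided 97.5% CI", and the rule is that "a CI entirely below 0.5 SD indicates noninferiority of the TECW Ed group within a 0.5 SD margin at the 0.025 level (1-sided". No covariate is named. The section then adds mixed models at weeks 2, 6 and 26, "controlling for site, tobacco or cannabis use status, demographics, and baseline level of the outcome variable".

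**Behavioural outcomes** (Secondary Outcomes). "We will compare the 2 groups with respect to mean engagement score at 6 weeks using a 2-sample *t* test". Tracker use is compared on the "mean number of Tracker reports between baseline and 6 weeks using a generalized linear model with negative binomial distribution and log link"; covariates for that model are neither listed nor excluded. Adjusted repeated-measures models are again added, with a baseline covariate for engagement only.

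**Randomisation** (Overview and Trial Design; Assignment of Interventions: Allocation). Allocation is 1:1 at each site, "in blocks stratified by tobacco or cannabis user status (any use in the past 30 days: yes or no").

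**Abstract, Methods.** For knowledge, perceptions and attitudes the abstract presents only the adjusted models as the planned analysis. No section says which analysis decides if the two disagree.

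**The concern.** Baseline engagement and the two stratification factors are known for the trial's participants, and the plan itself uses them in the additional engagement model. The t test that decides the engagement hypothesis uses none of them.

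The noninferiority comparison does use baseline, but only by subtracting it. That fixes the slope of the week-6 score on baseline at 1, whereas ANCOVA estimates it. It also leaves out site and use status.

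At stake is precision. Whether motivational and behavioural support changes behaviour beyond education alone is what the article presents as novel (Comparison With Prior Work), and engagement is one of the two outcomes that answer it. A modest effect on engagement could be missed for want of a covariate already in the database.

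A smaller matter is that the noninferiority rule does not say which SD scales the 0.5 SD margin, although the outcome has just been defined as a change.

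**Working it through.** **Inputs.** From Sample Size: 380 participants at week 6 (190 per arm), 340 at week 26 (170 per arm), margin or difference 0.5 SD, one-sided 0.025 or two-sided 0.05. The correlation r between baseline and week-6 score is not given, so 0.3, 0.5 and 0.7 are assumed. The score SD is assumed equal at both times and set to 1.

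**The plan's own figure.** Power = Φ(0.5/√(2/n) − 1.96).
- n = 190: 0.5/0.1026 − 1.96 = 2.91, power 99.8%.
- n = 170: 0.5/0.1085 − 1.96 = 2.65, power 99.6%.

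The stated figure of more than 95% is reproduced.

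**Per-person variance of each analysis.** Week-6 score alone: 1. Change: 2(1 − r). ANCOVA: 1 − r². The variance of change relative to ANCOVA is 2/(1 + r) = 1.54, 1.33 and 1.18.

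**Half-width of the interval**, 1.96 × √(2V/190), in score-SD units:

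| r | Week-6 score alone | Change | ANCOVA | ANCOVA narrower than change | ANCOVA narrower than week-6 alone |
|---|---|---|---|---|---|
| 0.3 | 0.201 | 0.238 | 0.192 | 19% | 5% |
| 0.5 | 0.201 | 0.201 | 0.174 | 13% | 13% |
| 0.7 | 0.201 | 0.156 | 0.144 | 8% | 29% |

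**Engagement power**, Φ(d/√(2V/190) − 1.96):

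| True effect d | t test | ANCOVA, r = 0.3 | r = 0.5 | r = 0.7 |
|---|---|---|---|---|
| 0.20 SD | 50% | 53% | 61% | 78% |
| 0.25 SD | 68% | 72% | 80% | 93% |
| 0.30 SD | 83% | 87% | 92% | 98% |
| 0.50 SD | 99.8% | 99.9% or more | 99.9% or more | 99.9% or more |

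**Noninferiority power**, true difference zero, margin 0.5 score SD. Change: 98.5%, 99.8% and above 99.9% at r = 0.3, 0.5 and 0.7. ANCOVA: at least 99.9% throughout. At lower correlations the change analysis gives 97.1% (r = 0.2) and 93.1% (r = 0).

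**Stratification factors alone.** In a simulation with 4,000 runs per setting and two factors of 0.3 SD each, constant over time, the unadjusted week-6 half-width rose only from 0.201 to 0.205. The change-score half-width did not move, because a constant stratum effect cancels on subtraction.

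**Margin.** The SD of change is √(2(1 − r)). Half of it is 0.59, 0.50 and 0.39 score SD at r = 0.3, 0.5 and 0.7. Sample Size equates 0.5 SD with 0.5 point on a 5-point scale whose SD is 1 point, which reads as the score SD. The rule in Primary Outcome does not repeat this, and knowledge is scored as percent correct.

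**The case against.** The strongest reply is that the adjusted analysis is already planned. Both outcome sections specify models with site, use status and demographics, and with baseline for the primary outcomes and engagement. Week 6 is one of their time points, and the abstract leads with them for knowledge, perceptions and attitudes. That is correct. What remains is rank: the tests attached to the hypotheses are the unadjusted ones, and only the raw difference carries a noninferiority rule.

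Several stronger readings are tempting, and the article does not support them.
- *That all the deciding comparisons ignore baseline.* Only the engagement t test does; a change score subtracts it. The within-arm test of change against zero is not a two-group comparison at all.
- *That the Tracker model is unadjusted.* Its covariates are simply unstated, which an article may leave to the full plan, and a baseline level is listed only for engagement.
- *That the trial needs about a third more participants.* The ratio 1.33 at r = 0.5 concerns precision. The plan makes no between-group superiority test on the primary outcomes, and noninferiority power is already ample.
- *That omitting the strata invalidates the tests.* The unadjusted standard error is conservative, and a wider interval makes noninferiority harder to claim, not easier.
- *That the margin is open-ended.* Sample Size points to the score SD; the rule needs to say so.

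It is also fair that at the 0.5 SD difference used for planning, the t test has 99.8% power. The gain is for smaller effects.

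**Conclusion.** The point holds as a matter of efficiency and of naming the deciding analysis, not of validity. It matters most for engagement: at a true effect of 0.3 SD, the t test has about 83% power, against about 87%, 92% and 98% with baseline adjustment at correlations of 0.3, 0.5 and 0.7. For noninferiority the interval would be about 19%, 13% and 8% narrower, with little bearing on the conclusion because power is already about 98% or more at those correlations. The stratification factors contribute little by themselves.

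These sizes rest on assumed correlations, equal SDs at the two times and 190 per arm. The direction does not depend on the value of r: baseline ANCOVA is never less precise than the change score or the week-6 score alone, apart from a trivial loss of degrees of freedom. The margin SD is a clarification.

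**What to change.** Before outcome data are analysed:

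1. Name the week-6 contrast adjusted for site, use status and the pre-randomisation score, from ANCOVA or the mixed model already planned, as the deciding analysis for engagement and for vape-related knowledge, perceptions and attitudes. Attach the noninferiority rule to that contrast.
2. Adjust cigarette items for site and use status only. Under Assessment Schedule their pre-education score is taken at week 2, after randomisation, when the added support has already begun.
3. State that the negative binomial Tracker model includes site and use status.
4. State in the noninferiority rule that 0.5 SD refers to the SD of the score, as Sample Size implies, and not to the SD of change.
5. Keep the raw difference in change and the t test as sensitivity analyses.

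No new data are needed; the covariates are already collected. Because data collection closed in June 2025, the cost is a dated and justified change to the analysis plan, recorded before results by arm are seen.

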#### Secondary Outcomes

The secondary outcomes are behavior changes. The hypothesis that the TECW Ed+ group, compared to the treatment-as-usual TECW Ed group, will display greater usage of the TECW Tracker and stronger engagement in supporting smoke- and vape-free regulatory efforts will be tested as follows. We will compare the TECW Ed+ group and the TECW Ed group with respect to the mean number of Tracker reports between baseline and 6 weeks using a generalized linear model with negative binomial distribution and log link. We will compare the 2 groups with respect to mean engagement score at 6 weeks using a 2-sample *t* test. We will also construct generalized linear mixed-effects repeated measures models to assess TECW-related behavior outcomes at weeks 1, 2, 4, 6, and 26 versus group, time, and a group × time interaction, controlling for site, tobacco or cannabis use status, demographics, and, for engagement, baseline level of the outcome variable. As an ancillary analysis, we will assess the link between awareness of campus TECW mitigation and behavioral outcomes among participants by including awareness as a covariate in models of Tracker report behavior. All randomized participants with week 6 data will be included in primary outcome analyses, and those who completed week 6 and month 6 will be included in follow-up analyses.

As an ancillary outcome, we will evaluate spillover behaviors such as off-campus TECW advocacy, and among tobacco users, proper disposal of e-waste and reported tobacco cessation by computing frequencies and percentages for each of these behaviors overall and by site and group at 6 weeks and 26 weeks. Furthermore, to describe changes in campus TECW, we will use generalized linear mixed models of the number of TECW reports per month to estimate trends over time and association with environmental scans, overall and among study participants, assuming autoregressive correlation from month to month at each site and negative binomial distribution with log link. Separate models will be created for different types of TECW, and interactions between site and time will be included to assess differences in trends between sites.

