### Intervention Description

#### Overview

Both groups receive education about TECW at baseline and week 2 visits by viewing videos and receiving a link to the TECW Tracker at baseline and week 2. The intervention group receives education plus motivational enhancement and behavioral support for using the TECW Tracker. Both groups receive a check-in text at week 1 and week 4 containing a brief assessment and a reminder for their next study visit. The intervention group’s text includes feedback about the positive environmental impact of making TECW reports and offers assistance with the Tracker if no reports had been made (Figure 2).

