#### Motivational Enhancement and Behavioral Support

Each study visit in which education is provided (baseline and week 2) contains additional motivational enhancement or behavioral support for the TECW Ed+ group. Each text message (week 1 and week 4) provides a brief assessment and reminder of the next study visit as well as additional motivational enhancement and behavioral support for the TECW Ed+ group. The week 6 visit provides another motivational booster to the TECW Ed+ group. Table 1 presents the components and timing of the motivational enhancement and behavioral support.

**Table 1 table1:** Timing of motivational enhancement and behavioral support components.

Component	Baseline	Week 1	Week 2	Week 4	Week 6
Discuss video takeaways	✓		✓		
Discuss values and connect to Tracker	✓				
Instruction in using TECW^a^ Tracker	✓		As-needed^b^		
Offer assistance with using Tracker		As-needed^b^		As-needed^b^	
Motivation and confidence for using Tracker	✓				
Action planning for using Tracker	✓		✓		
Summary of Tracker reports and why reporting is useful		✓	✓	✓	✓

^a^TECW: tobacco, e-cigarette, and cannabis waste.

^b^Provided to those who have not made Tracker reports.

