#### TECW Tracker Use

Awareness of a tool to report TECW on campus and use of the tool is assessed with yes or no questions [30]. Participant Tracker use is also measured objectively based on participant ID–linked TECW Tracker usage data.

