#### Environmental Impact of TECW Campus Intervention

Counts of TECW by product type as well as “looks good” reports are tabulated for each campus location on a weekly basis from the Esri ArcGIS–based TECW Tracker reports from participants and nonparticipants (eg, general campus community) through TECW Tracker. Counts of TECW by product type are also tabulated from objective environmental scans conducted by site staff.

As a secondary outcome, we assess the link between awareness of campus TECW mitigation and behavioral outcomes. Two items to assess this include: “How aware were you of how your Tracker reports were addressed?” (Response options include not at all, a little, moderately, and very aware), and “How satisfied were you with campus actions taken in addressing TECW?” (Response options range from very dissatisfied to very satisfied). An open-ended prompt follows for those who report dissatisfaction.

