#### Attributions of Intervention Components

Following the week 6 survey, those in the TECW Ed+ group are administered another survey assessing their attributions of two intervention components: (1) talking with the study team and (2) receiving feedback about actions taken from TECW reports. They rate their agreement with the following three questions on a 5-point scale, ranging from strongly disagree to strongly agree: [Intervention Component]: (1) taught me new information about TECW, (2) increased my desire to do something to reduce TECW, and (3) increased my desire to report TECW.

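### The ancillary Tracker model adjusts report counts for awareness of how those same reports were addressed, so it can show neither an effect of awareness nor a valid Ed+ effect

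*Protocol article*

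**What the plan says.** In the Secondary Outcomes part of Statistical Methods, the protocol article states: "As an ancillary analysis, we will assess the link between awareness of campus TECW mitigation and behavioral outcomes among participants". The method is given in the same sentence: "by including awareness as a covariate in models of Tracker report behavior". The Tracker models described just before it have group as a term. The main comparison is a negative binomial model, log link, of reports from baseline to 6 weeks. The repeated-measures model has group, time and their interaction.

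The section on the environmental impact of the campus intervention defines awareness by one four-level item, "How aware were you of how your Tracker reports were addressed", and calls this link a secondary outcome. The outcome in the Tracker models is the same person's own reports: "Participant Tracker use is also measured objectively based on participant ID–linked TECW Tracker usage data".

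Feedback on reports belongs to the Ed+ arm:
- The Overview of the intervention says that the Ed+ "text includes feedback about the positive environmental impact of making TECW reports".
- Table 1 schedules "Summary of Tracker reports and why reporting is useful" at weeks 1, 2, 4 and 6.
- The section on attributions names "receiving feedback about actions taken from TECW reports" as one of two Ed+ components that participants rate.
- The Blinding section says that "providing feedback to the TECW Ed+ group is a component of the intervention".

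**The concern.** The covariate is tied to the outcome. The item asks, in the past tense, what became of the respondent's own reports. A person who made none has nothing to be aware of, and a person who made several has had more chances to see or hear a response. A regression of the report count on this item will tend to show an association even if awareness never changed anyone's behaviour.

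The covariate is also tied to the arm, because only Ed+ participants are given feedback on their reports. Conditioning on a variable that both outcome and arm affect biases the group coefficient in that model.

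Two readings of the result are at stake: that awareness of mitigation leads students to report more, and that the Ed+ effect shrinks or changes once awareness is accounted for. Neither could be taken from this model.

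**Working it through.** The article gives no figure for this analysis, so there is none to reproduce. The check has two parts.

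**1. Time order and dependence, from the text.** Participants enter a study ID when they report, and randomisation follows the baseline survey. An item about how ID-linked reports were addressed must therefore come after randomisation and after at least some reporting. Feedback is given in Ed+ only. Both paths, reports to awareness and arm to awareness, are thus plausible from the document itself. The article states no lag, no restriction to reporters and no mediation framework.

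**2. Size, by simulation.** From the Sample Size section: 400 × 0.95 = 380 participants at week 6, or 190 per arm. Assumed, because the document does not give them: control mean of 2 reports, dispersion 1, and awareness generated after the reports, so that it has no effect on them:

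L = bR·ln(1 + reports) + bG·Ed+ + N(0,1), cut into four levels.

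The model is log E(reports) = β0 + β1·Ed+ + β2·awareness, negative binomial, 400 runs per scenario. Without the awareness term, the group rate ratio came back at about 1.0, 1.5 and 2.0 in every scenario. With it:

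| bR | bG | Group RR, true 1.0 | Group RR, true 1.5 | Group RR, true 2.0 | RR per awareness level |
|---|---|---|---|---|---|
| 0 | 0 | 1.00 | 1.51 | 2.01 | 1.00 |
| 0 | 0.5 | 1.01 | 1.49 | 2.02 | 0.99 to 1.00 |
| 0.5 | 0 | 1.00 | 1.44 | 1.85 | 1.40 |
| 0.5 | 0.5 | 0.86 | 1.23 | 1.60 | 1.40 to 1.41 |
| 0.5 | 1 | 0.72 | 1.03 | 1.32 | 1.40 to 1.43 |
| 1 | 1 | 0.61 | 0.81 | 1.01 | 1.83 to 1.90 |

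- *Awareness term.* P<.05 in 100% of runs whenever bR > 0, against about 5% when bR = 0.
- *Group term.* With a true ratio of 1.0, the last three rows gave a falsely significant group term in 21%, 63% and 97% of runs.

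**Sensitivity.** A second set of assumptions used means of 1.5 and 3.0 (true ratio 2.0), dispersion 2, and an Ed+ effect on awareness in reporters only. The adjusted group ratio was:
- 0.89 to 0.92 with strong paths (bR 0.9, bG 0.8);
- 1.41 with 0.5 and 0.5;
- 1.77 with 0.3 and 0.3;
- 1.84 with 0.2 and 0.2;
- 2.37 when reports lowered awareness (bR −0.3, bG 0.8), with an awareness ratio of 0.68. A separate run with reports lowering awareness gave 2.23.

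Under these assumptions many participants have no report. P(0) = (1 + 2μ)^(−1/2), which is 0.50 at μ = 1.5 and 0.38 at μ = 3.0, about 44% overall. The simulations give these people an awareness score although the item has no clear meaning for them. Among reporters only, the strong-path case gave a group ratio of 1.14 and an awareness ratio of 1.55. That restriction itself changes the group ratio.

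**The case against.** The strongest reply is that the plan claims little here. The analysis is labelled ancillary and speaks of a link, with no causal or mediation claim. That stands, and it limits the weight of the point. It does not remove it: a link that largely follows from the item's wording says little even as description, and the measurement section calls the same link a secondary outcome.

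A reader might infer that the trial's Tracker result is compromised. The document does not support this. The Ed+ versus Ed hypothesis is tested in a separate negative binomial model without awareness, and nothing says that a group effect will be taken from the adjusted model.

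A reader might also infer that adjustment must erase or reverse the Ed+ effect. That is not supported either. There is no distortion if reports do not affect awareness, and little if Ed+ does not. The sign turns if reporting lowers awareness, for example because reports seem to go unanswered. A ratio below 1 from a true 2.0 appeared only with strong assumed paths.

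Finally, the article does not say when the item is asked, and a full analysis plan might specify a lagged model or handle non-reporters. That is possible. But the specification that is stated, awareness as a covariate in the Tracker report models, carries no such restriction, so the criticism is of what is written.

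**Conclusion.** The point holds for the ancillary analysis only. As specified, it conditions report counts on a post-randomisation variable that plausibly results from both reporting and Ed+ feedback. If reports raise awareness, a positive association is expected without any effect of awareness on reporting (1.40 to 1.90 per level in the main simulation). The group coefficient in that model is not a valid Ed+ effect. A true rate ratio of 2.0 became about 0.9 to 1.9 when reports and Ed+ both raised awareness, and above 2 when reports lowered it.

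These figures depend on assumed means, dispersion and path strengths that the document does not give. They show that the distortion can be material, not what it will be in this trial. The problem of interpretation rests on the item's wording and the Ed+ components, not on those assumptions. The planned main Tracker comparison is unaffected.

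**What to change.** Amend the wording of the ancillary analysis before results are reported:

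1. Take the Ed+ versus Ed Tracker effect only from models without awareness.
2. Do not enter awareness as a covariate for reports made before or at the time it was measured.
3. Report the awareness-reports link descriptively, by arm, among participants with at least one report, and state when the item was asked.
4. Optionally, if awareness was measured by week 6, model reports from week 6 to week 26 on it, adjusting for arm, site, use status and prior report count. Label this observational and interpret no group effect from it, because the reporter subset is itself selected after randomisation.

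The cost is a change of wording, plus a smaller subset and a wider interval for an ancillary result. No new data are needed for steps 1 to 3.

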#### Missing Data

Although our follow-up rates in previous studies have typically exceeded 80%, missing data will arise for a variety of reasons (item nonresponse, etc). Prior to testing primary hypotheses, we will conduct exploratory analyses to determine if baseline characteristics predict patterns of missing data. Any significant (*P*<.10) predictors of missing data will be included as covariates in models above and used with multiple imputation methods [75,76] for evaluating model estimates.

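### Analysis sets defined by attendance after randomisation sit badly with the planned repeated-measures models and leave the scope of multiple imputation unsettled

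*Protocol article*

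**What the plan says.** The rule is in the protocol article, Statistical Methods, at the end of the first paragraph under Secondary Outcomes: "All randomized participants with week 6 data will be included in primary outcome analyses, and those who completed week 6 and month 6". The second half of that sentence sets the later analyses: "those who completed week 6 and month 6 will be included in follow-up analyses".

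Four other places bear on it:

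- **Primary Outcome** plans, besides the change-score comparisons, "mixed-effects repeated measures models to assess knowledge, perceptions, and belief outcomes at weeks 2, 6, and 26". Secondary Outcomes plans similar models for behaviours at weeks 1, 2, 4, 6 and 26.
- **Missing Data** opens with "Although our follow-up rates in previous studies have typically exceeded 80%, missing data will arise for a variety of reasons (item nonresponse, etc". It goes on to say that "predictors of missing data will be included as covariates in models above and used with multiple imputation methods".
- **TECW Tracker Use** states: "Participant Tracker use is also measured objectively based on participant". The sentence goes on to name usage records linked to the study ID, so this outcome does not need a visit.
- **Sample Size** sets the planned losses: "assuming a sample size of 380 at 6 weeks (95% retention) and 340 at 26 weeks (85% retention".

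The article reports 406 students enrolled and randomised 1:1. It nowhere says that all of them are analysed in the arm to which they were assigned.

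**The concern.** Whether someone attends week 6 or month 6 is decided after randomisation and may depend on the arm. Conditioning on it means that the groups compared need not be those that randomisation made comparable.

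The rule also removes data that the planned models could use. A participant with week 2 data but no week 6 data has something to contribute to a repeated-measures model. So has one with week 26 data who missed week 6. The attendance rules exclude the first from primary outcome analyses and the second from both sets.

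Finally, the rule leaves the imputation plan without a clear scope. If imputation is meant to cover missed visits, the week 6 rule takes out the people whose visits would be imputed. If it covers only skipped items among attenders, the article does not say so. Two analysts could reasonably build different analysis sets from these sections.

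**Working it through.** **Inputs.** From Sample Size: 400 planned (200 per group), 380 at week 6, 340 at week 26, and a 0.5 SD margin. The dropout splits and the outcome deficit among dropouts below are assumptions; the article gives neither.

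**1. The plan's own figures reproduce.** The article gives no base rate, so proportions are taken as symmetric about 0.5.

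| Per group | Detectable difference, 80% power (with continuity correction) | Power for 0.5 SD |
|---|---|---|
| 190 (week 6) | 14.3 points (14.9) | 99.82% |
| 170 (week 26) | 15.1 points (15.7) | 99.60% |

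These agree with the stated 15-16 points and more than 95% power.

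**2. Who is left out, at planned retention.**

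- Week 6 rule: 400 − 380 = 20 (5%), with any week 2 data they gave.
- Both-visits rule: the overlap of the two attendance groups is at least 380 + 340 − 400 = 320 and at most min(380, 340) = 340. So 400 − 340 = 60 to 400 − 320 = 80 are left out (15-20%).
- Observed week 26 data dropped only because week 6 was missed: 340 − 340 = 0 to 340 − 320 = 20 participants.
- The remaining 400 − 340 = 60 have no week 26 data to discard.

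**3. Effect on power.** With all 400 treated as fully informative (an upper bound), the detectable difference is 14.0 points (14.5 with correction) and power for 0.5 SD is 99.88%. At the smallest both-visits set, 160 per group, the figures are 15.6 points (16.2) and 99.40%. Power is not the issue.

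**4. Possible bias in a mean.** If dropouts score 0.5 SD below completers, an arm's completer mean exceeds its full mean by 0.5 × (loss fraction). The shift in the Ed+ minus Ed contrast is therefore 0.5 × (loss in Ed+ − loss in Ed).

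- Week 6, 8% v 2% (averaging the planned 5%): 0.5 × (0.08 − 0.02) = 0.03 SD. The standard error is √(2/190) = 0.103 SD, so this is about 0.3 SE, or 0.03/0.5 = 6% of the margin.
- Week 26, 20% v 10% (averaging the planned 15%): 0.5 × (0.20 − 0.10) = 0.05 SD. The standard error is √(2/170) = 0.108 SD, so this is about half an SE.
- Equal loss with equal deficit: 0.

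Equal loss is not a full safeguard. If the between-arm difference among those excluded were 0.5 SD away from that among those included, the shift would be 0.05 × 0.5 = 0.025 SD at week 6. In follow-up it would be 0.15 × 0.5 = 0.075 to 0.20 × 0.5 = 0.10 SD.

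**5. Direction.** Noninferiority of Ed requires the interval for Ed+ minus Ed to lie entirely below 0.5 SD. Greater loss of low scorers from Ed+ raises that difference, so it works against declaring noninferiority. Greater loss of low scorers from Ed would do the opposite.

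**The case against.** Much can be said for the plan.

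- **Imputation still has a use.** Among week 6 attenders it can fill skipped items, missing week 2 scores and missing covariates, and item nonresponse is the only cause the article names. A reader might infer that the completer rule and the imputation plan cannot both be followed; the text does not support that. What stands is that Missing Data opens with follow-up rates and gives item nonresponse only as an example, so its scope is unreconciled with the rule.
- **The week 6 rule is worded for primary outcomes.** These are knowledge, perceptions and attitudes; Tracker use is secondary, and its analysis set is not separately stated. A reader might infer that Tracker counts will be restricted to attenders and the rate ratio inflated. The article does not say this. Applying month 6 losses to a count that ends at week 6 would also be wrong, since someone lost later may have reported during those weeks.
- **A change score at week 6 needs week 6 data.** For that comparison the rule partly describes who can contribute without a model or imputation. This does not justify the both-visits rule or the loss of partial records from the mixed models.
- **Differential loss is not shown.** Both arms have the same visits and text check-ins. The extra content in Ed+ could improve retention as easily as reduce it. The splits above are illustrations only.
- **Detail may sit in an analysis plan not shown.** That applies to how the imputation model is built and how predictors of missingness are screened, so neither is raised here. It does not apply to the analysis sets, which the article states outright.

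**Conclusion.** The concern holds in a limited form. The article defines its analysis sets by attendance after randomisation, does not reconcile them with its repeated-measures models or its imputation plan, and nowhere commits to analysing all 406 as assigned. At planned retention this leaves out 5% at week 6 and 15-20% in follow-up, including up to 20 people with usable week 26 data.

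The likely distortion is small at week 6, where the hypotheses are set: about 0.03 SD under the assumed 8% v 2% split. It is somewhat larger at week 26, about 0.05 SD under 20% v 10%. Both rest on an assumed 0.5 SD deficit among dropouts. In those scenarios the week 6 error makes noninferiority harder to show, so they give no ground for inferring a false noninferiority claim. Power is essentially unaffected.

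This should be fixed, because the stated rule is weaker than an available alternative that costs almost nothing. At 5% planned week 6 loss it does not threaten the trial's main conclusion.

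**What to change.** Replace the sentence under Secondary Outcomes with a statement that:

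1. all 406 randomised participants are analysed in their assigned arm;
2. survey outcomes use the mixed models on all available post-baseline records, with no requirement to have completed both week 6 and month 6;
3. the baseline-to-week-6 Tracker comparison counts ID-linked reports for every randomised participant, whether or not they attended;
4. multiple imputation covers missed visits as well as item nonresponse;
5. the two completer sets are kept as sensitivity analyses.

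The cost is a change of wording and a little programming, with no new data. The article expected analysis to begin in late 2025. The change should be dated and made before results by arm are seen; if they have been seen, both versions should be reported and the timing stated.
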